**Figure 1 figure1:**
[figure not shown]
Planned study flowchart.

### Intervention Group

After completing randomization at baseline, schools located in the intervention group will be invited to participate in the “Healthy Cafeteria: we support this idea!” Program (*Cantina Saudável: a gente apoia essa ideia!* originally in Brazilian Portuguese). This is an educational intervention consisting of a 160-hour asynchronous distance-learning qualification course using the Moodle platform. Each school from the intervention group will also have a support group on WhatsApp (Facebook Inc, Menlo Park, CA), including all the participants enrolled by the school. The course will have a duration of 10 weeks, with a workload of 16 hours per week.

The target audience of the intervention will be the owners and people in charge of the cafeterias, food handlers, principals, vice principals, teachers, pedagogical coordinators, dietitians, representatives of students’ parents, and students over 16 years old. Each week, a course module will be available on a distance-learning platform through lectures, texts, videos, and activities. Moreover, a discussion forum will be developed for each module to encourage learning, share experiences, provide support, and instigate community interaction. In each module, we will provide practical activities to be held in school cafeterias. Our teaching strategy will implement context-based and problem-solving activities. The modules will be made available in stages, so that the workload is fulfilled according to the plan. In addition, the modules will be available until the end of the course, and it is not necessary to meet fixed hours and deadlines for most course activities. This flexibility of distance learning allows participants to adapt their studies according to their routine.

The principal of each school in the intervention group will receive 2 phone calls during the intervention: the first one in the 4th week and the other in the 7th week. Both calls will be for support and follow-up for the intervention program. Calls will last approximately 5 minutes, and we will ask the director if their participants need any instructions or assistance. In addition, participants will be able to chat with a tutor throughout the intervention via chat using the Moodle platform and WhatsApp. These strategies will be used to avoid participant drop-outs.

The material used as a basis for developing the education intervention will be the book “Manual das cantinas escolares saudáveis: promovendo a alimentação saudável” (Guide of the Healthy School Cafeteria: Promoting the Healthy Food), developed by the Ministry of Health of Brazil [47]. This document guides the implementation of the school cafeterias throughout Brazil. The material was adapted according to the characteristics of the region of Brazil where the courses will be developed. The course will consist of 8 modules, depicted in Textbox 1.

Components of the intervention program for a healthier school cafeteria.Module 1 - Starting the healthy school cafeteriaGoalsTo present relevant information about the health of children and adolescentsTo study how schools and cafeterias can promote healthy and proper eatingTo understand the importance of implementing healthy school cafeterias and reasons to changeTo get to know the current laws that provide for regulation in the supply of food in school cafeteriasIntervention items and componentsExpository classes, using slides, with an introduction of the theme and concepts for implementing a healthy cafeteria in the school settingCurrent legislation regulating the supply of food in school cafeterias in BrazilA video with a report on the law of cafeterias in southern BrazilHands-on activity: participants are instructed to check what is sold at schoolModule 2 - What is healthy eating?GoalsTo get to know the concept of adequate and healthy eatingTo learn what is healthy eating based on the Brazilian Population Food GuideIntervention items and componentsExpository class, using slides, on the importance of healthy eating in schools and the concept of adequate and healthy eatingVideos about the concept of healthy eatingIndication of a film about the childhood obesity epidemicHands-on activities: participants are instructed to classify food sold in the cafeteria based on the concepts learned, create a campaign to encourage the consumption of healthy foods in school (eg, “buy 10 healthy items, get the 11th item for free”; “collect and exchange your points for products”). In addition, teachers are instructed on how to apply the concepts of healthy eating in the classroomModule 3 - Cafeteria and industrialized foodsGoalsTo get to know the effects of the consumption of industrialized foods on the student's healthTo learn how to choose foods by reading labels and nutritional informationIntervention items and componentsExpository class, using slides, on industrialized foods and their effects, involving the reading of food labelsEducational videos that teach the participant to choose healthy foods by reading the labelsSuggesting an app to aid in healthy choices: DesrotulandoHands-on activity: participants are instructed to remove from the cafeteria foods they consider unhealthyModule 4 - Healthy snacksGoalsTo provide suggestions for healthy and creative snacks to be offered in school cafeteriasIntervention items and componentsExpository class, using slides, with suggestions for healthy and creative snacksA video about healthy snacks at schooleBook with healthy recipes for school cafeteriasHands-on activity: participants are instructed to develop a menu with healthy snack options for the cafeteria.Module 5 - Food hygieneGoalsTo learn about the importance of adopting good practices in food handling to ensure the sanitary quality and safety of food sold in the school cafeteriaIntervention items and componentsExpository class, using slides, about food hygieneVideos on food handler hygiene and the correct way to sanitize vegetables and fruitsHands-on activities: participants are instructed to record a video sanitizing their hands, take a selfie wearing a hygiene cap, and draw up a poster to prohibit unauthorized people from entering the cafeteria.Module 6 - Food and nutrition educationGoalsTo present educational strategies and activities to promote adequate and healthy eating in the school settingIntervention items and componentsExpository class, using slides, about food and nutrition education activitiesA video addressing the importance of promoting adequate and healthy eating in the school curriculumHands-on activity: participants are encouraged to develop a food and nutrition education activity based on the content learned.Module 7 - How to profit from healthy school cafeterias and successful experiencesGoalsTo present strategies on how to profit from the sale of healthy foods and show successful experiences in planning and implementing the healthy school cafeteriaIntervention items and componentsExpository class, using slides, on strategies to profit from healthy school cafeteriasVideos showing successful experiences in the implementation of a healthy school cafeteriaHands-on activity: participants are instructed to create a healthy recipe with a creative name and disseminate it to the school community.Module 8 - Schedule of activities and how to keep the school cafeteria healthyGoalsTo propose a schedule of actions that must be carried out for the school to implant and maintain a healthy school cafeteriaIntervention items and componentsExpository class, using Microsoft PowerPoint, with actions that must be performed in school for the implementation and maintenance of the healthy school cafeteriaHands-on activity: participants are encouraged to reflect on the changes made in the cafeteria (positive and negative points) during the intervention, including what still needs to be improved and what goals will be set to keep the school cafeteria healthy.

All components of the program will be offered to all participants in the school community because the content of the program does not require specific knowledge or prior training, meeting the requirements of the book on which it was based [47]. No payment nor refund will be made for cafeterias and schools to participate in the study. Local law does not allow individuals to participate in research for remuneration [48]. Schools that agree to participate will be aware of the need for the participants to dedicate time and adapt their work routine during the intervention period. Although the course includes 160 hours, this number of hours does not refer only to attending classes, but rather considers engagement in all activities necessary for the intervention process, such as talking to the school staff and performing the proposed tasks and assignments. At baseline and after follow-up, cafeterias will receive feedback on their performance, and the situation will be assessed.

There was a post hoc change in the protocol of this study in relation to what was originally planned in the trial registry. Initially, we stipulated that the intervention program would be delivered in 160 hours over 20 weeks, therefore, with a workload of 8 hours per week. It was also foreseen that the course would have 140 hours in distance mode and 20 hours of in-person mode. However, in new planning, we defined that the program would be delivered only in the distance mode and in a shorter period of time, with a weekly workload of 16 hours over 10 weeks. We justify this because of the limited funding available and the considerable geographical distance between the locations of participating schools.

### Control Group

The control group will not receive any type of active intervention. After data collection is completed at baseline, schools from the control group will receive a printed copy of the book “Guide of the Healthy School Cafeteria: Promoting the Healthy Food” developed by the Ministry of Health of Brazil [47]. At baseline and after follow-up, cafeterias will receive feedback on their performance, and the situation will be assessed.

### Data Collection and Management

The study will be conducted in 3 stages, depicted in Figure 2. Data to assess outcomes will be collected at baseline and after follow-up. Not all interventions will be carried out in a contiguous and parallel time for all locations since the schools to be selected may be very distant geographically, and this will require more effort and time from researchers.

**Figure 2 figure2:**
[figure not shown]
Study overview.

Researchers responsible for collecting data on site will be previously trained and will receive a guidance manual with information on the collection order, data completeness, researcher’s characterization and identification, behavior, actions, language, and guidelines on the observation of hygienic conditions. The investigation of the profile of school cafeterias will be carried out through a cross-sectional assessment using a printed questionnaire with the owners or people in charge of the school cafeterias and the school directors. This characterization of the study population will be done at the beginning of the study, simultaneously with the data collection of baseline variables, and it will be carried out before randomization by the researcher tasked with the collection of outcome measures. The data on the profile of the school and the cafeteria will be collected through a face-to-face interview with the principal and head of the cafeteria, respectively, using a printed demographic questionnaire.

The questionnaire for collecting demographic data will be based on studies by Giacomelli [49] and Porto et al [50]. The following information will be included: characterization of the school, type of management, educational stage, number of students, presence of school meals, type of cafeteria management, number of people working in the cafeteria, opening hours, number of snacks served, place of production of snacks, aspects involved with the choice of food offered, presence of other types of sale within the school, and presence of a dietitian. The questions related to the composition of the menu offered in school cafeterias according to the level of food processing will be based on the recommendations of the Food Guide for the Brazilian Population [51] and on the studies by Wolfenden et al [52] and Williams et al [25]. Meanwhile, the questions related to hygienic conditions will be obtained from the assessment frameworks already developed and validated by the Brazilian Health Regulatory Agency, which is equivalent to the US Food and Drug Administration [31,53]. Data entry from all instruments will be performed in parallel and with redundant copies to verify the integrity and concordance of collected data.

We will analyze the fidelity and dose of the intervention based on the reports of participants' usage of the Moodle platform. This includes access logs with the day and time that the participant accessed the platform, all actions performed, list of activities and assignments, number and history of views, the fulfillment of activities, dwell time, and other information. In addition, participation will be verified based on the history of submitted assignments and participation in the discussion forums. The assessment of the feasibility and acceptance of the intervention will be measured based on the changing effects of the assessed outcomes, usage reports of Moodle, and an assessment of the participants' acceptance and their perception of the course, through an online retrospective questionnaire (Multimedia Appendix 1) applied at the end of the program.

### Outcome Measures

We aim to verify the efficacy of an educational intervention program to improve the hygienic conditions and the composition of the menu offered in school cafeterias in the state of Rio Grande do Sul, Brazil. The efficacy of the intervention will consider 2 primary outcomes: (1) composition of the menu offered (percentages of fresh, processed, and ultraprocessed foods) and (2) assessment of hygienic conditions concerning good practices in handling food. The secondary outcome will be a score calculated according to the level of processing of food sold. These variables will be collected at baseline and immediately after the intervention.

#### Primary Outcomes

The assessment of the impact of the intervention on the composition of the menu offered in school cafeterias will be based on similar Australian studies [25,54]. The assessment of the school cafeteria menu composition will be determined by counting all items sold and the percentages of food classified according to the level of industrial processing proposed by the Food Guide for the Brazilian Population [51] and Monteiro et al [55]. A modified version of these references was used for this research. Group 1 (F*fresh*) includes fresh foods, minimally processed and culinary preparations without the addition of culinary ingredients (salt, sugar, oils, fats, or other ingredients). Group 2 (F*process*) includes processed foods and culinary preparations with culinary ingredients. Group 3 (F*ultra*) includes ultraprocessed foods. The culinary ingredients group proposed by Brazil [31] was excluded from the classification because the cafeterias do not sell these foods in isolation. Two properly trained dietitians will carry out this assessment using pen and paper. In case of divergence, a third dietitian will be consulted.

Good practices in food handling are a set of procedures that food services implement to ensure food quality to the consumer, minimizing possible harm to health, especially that caused by foodborne diseases. In this sense, there is a need to assess and classify the food sold according to the characteristics that include the amount of microbial and chemical contamination [56]. To collect data regarding hygienic conditions, we will use an instrument that has been validated by the National Health Surveillance Agency [57], which is based on Brazilian legislation, Regulatory Ordinance 817, published on May 10, 2013, by the Ministry of Health [56]. This legislation is composed of 51 items from 9 categories: water supply; building structure; cleaning of facilities, equipment, furniture, and utensils; control of vectors and urban pests; food handlers; raw material, ingredients, and packaging; food preparation; storage, transport, and display of prepared food; and liability, documentation, and registration.

The assessment of the hygienic conditions of the cafeterias consists of a continuous scoring system that ranges from 0 (less severe) to 2498.89 (more severe). The score will be assigned when the evaluated cafeteria does not meet some of the requested requirements, so the higher the score, the greater the number of nonconformities verified and the worse the performance of the establishment [58]. The scores for each of the 51 items checked will be defined based on risk criteria, in order to identify those that have the most direct impact on the quality of food and on the health of consumers. In the score, the Impact Index will be used, representing the importance in the prevention of foodborne diseases, as well as the Factor Load of the items, as validated by the National Health Surveillance Agency [57]. This assessment will take place through an onsite inspection carried out by a trained dietitian using a printed checklist.

#### Secondary Outcome

To assess the impact of the intervention on the food sold in the cafeteria, we have prepared a score that can be calculated based on the frequency of food available for sale and its classification according to the level of industrial processing proposed by Brazil [51] and Monteiro et al [55]. This score was developed due to the lack of a standard method for analyzing food in the school environment [59] and was also based on similar Australian studies [25,26]. Therefore, in addition to evaluating the composition of the menu offered in primary outcomes, we also chose to develop an equation that uses the frequency of each type of food but makes these variables continuous for a secondary outcome.

After data collection, all types of food and drinks sold in the cafeterias will be classified according to their level of processing. In the second stage, for each cafeteria, the frequency of items available in each category will be counted, multiplied by the standardized weight for the Group of fresh foods, Group of processed foods, and Group of ultraprocessed foods, which are +1, 0, and -1, respectively, as they are healthy, neutral, and unhealthy, respectively.

Equation (1) is used to calculate the score of the cafeteria for the level of food processing, where F*fresh* = frequency of fresh food items; F*process* = frequency of processed foods; F*ultra* = frequency of ultraprocessed foods; n = total number of items sold in the cafeteria, achieved by multiplying the frequency of food in each category by its corresponding weight, added to the values and dividing by the total number of items sold in the cafeteria. The score formula 50R + 50 is used to obtain scores for each establishment.

The score can vary on a scale of 0 to 100 points, where 50 is the midpoint. Thus, a cafeteria that offers healthy (fresh) and unhealthy (ultraprocessed) food in equal quantities will receive an average score of 50 points and will be considered a neutral cafeteria. Cafeterias that reach a score below 50 points have a greater predominance of ultraprocessed foods (ie, a greater offering of unhealthy foods). In summary, higher scores reflect better food quality in the school cafeterias.

### Statistical Analysis

We will consider the 2 primary outcomes and the secondary outcome: composition of the menu offered (ordinal categorical data), assessment of hygienic conditions concerning good practices in handling food (continuous variables), and the score for the level of processing of food sold (continuous variables). The baseline characteristics of the school and the cafeteria will be presented in conventional descriptive statistics. Continuous variables will be presented as means and standard deviations for symmetric data or medians and interquartile ranges for asymmetric data, while categorical variables will be presented as frequencies and percentages. All outcomes will be analyzed as intention-to-treat and per-protocol. The intention-to-treat analysis will include all participants according to their original group assignment, regardless of what happened later. The per-protocol analysis will consider only those participants who comply with the protocol in terms of eligibility, interventions, and evaluation of results [38]. Unadjusted and adjusted estimates allowing for the potential confounding effects of all minimization factors will be presented for primary and secondary endpoints. Multiple imputation will be used to deal with missing data [60].

For the analysis of continuous data (hygienic conditions and level of processing of food sold), analysis of covariance or a generalized linear model with an appropriate link function will be used, depending on the data characteristics. The outcomes will be assessed by comparing the mean changes (delta) between baseline and follow-up values between the groups, adjusting for the baseline value of the outcome. For the analysis of ordinal categorical data (menu composition and percentages of each type of food), we will use an ordinal logistic regression model to assess between-group differences at follow-up, adjusting for the baseline value of the outcome. All data will be analyzed using the statistical software SPSS 26.0 (IBM Corp, Armonk, NY) and R Software 3.5.0 (R Development Core Team). The statistical level of significance considered will be *P*<.05 for a confidence interval of 95%.

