### Recruitment and Eligibility Criteria

A total of 330 schools will be assessed for eligibility to participate in the study. The definition of these schools will be obtained through data from the Education Department of the State of Rio Grande do Sul [40]. Confirmation or updates of the existing data will be verified by phone calls to all schools. We will invite to participate elementary and high schools of the public and private sectors located in the Cidadania Noroeste Colonial region, State of Rio Grande do Sul, Brazil, which total 36 municipalities according to the last official census [41].

Schools will be eligible to participate if they have a school cafeteria and they show interest in participating in the research upon signature of a consent form. Schools with exclusive care for children with special needs will be excluded, as they require a different standard of care. Schools will not be excluded based on other characteristics such as size, socioeconomic indicators, and others. Eligibility criteria will be applied prior to randomization.

Eligible schools will be personally invited to participate in the study by the research team. This strategy will be used to ensure the desired sample size. The school principal will sign a consent form for participation. In the case of outsourced cafeterias, we will request the consent of its owner. Each school will nominate its representatives to participate in the study. The principal will be responsible for obtaining the consent of the nominated members.

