### Sampling

The sample size calculation was based on primary outcomes. For a significance level of 5% and statistical power of 90% to detect an effect magnitude (*d*) of 0.90, 54 schools will be needed, considering 27 for the intervention group and 27 for the control group. We considered a 10% sample loss to estimate an increase in the sample size. The estimated number of participants required to achieve the study objectives was also based on the study by Nathan et al [24], which aimed at examining whether a theoretically conceived multicomponent intervention was effective in enhancing the implementation of a healthy cafeteria policy in Australian primary schools. The sample size calculation was performed using the Power and Sample Size software (HyLown Consulting LLC, Atlanta, GA).

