### Randomization and Allocation

Randomization will use a minimization process [42] to balance the number of schools between the 2 groups. This approach ensures an excellent balance between groups for several prognostic factors, even in small samples. According to Egbewale [43], the minimization process makes the evaluated groups similar in important characteristics, mainly in trials that involve a small sample and have several prognostic factors to be balanced [38,44]. This procedure decreases the chances of significant discrepancies in baseline prognostic factors that may occur at random [45]. Minimization also controls the imbalances in baseline variables more efficiently than simple randomization, since, in small samples, simple randomization can produce a biased and misleading effect [43,46].

To maintain the balance between groups and prevent disproportionate distribution from occurring, 4 predictors of interest for the allocation will be considered: city, cafeteria administration (school-owned versus outsourced), school scope (public versus private), and the number of students (<500 students versus ≥500 students). An independent researcher will perform the randomization by minimization using a computer-generated technique in SPSS 26 (IBM Corp, Armonk, NY), avoiding possible influence on the allocation. The randomization unit will be schools with cafeterias.

As it will be an educational intervention, the researchers in charge of administering the interventions and assessing the outcomes will not be able to be blinded. Therefore, to avoid interference between the control and intervention groups, blindness will be arranged for the statistician in charge of data randomization and analysis. Participant flow during each stage of the study can be seen in the estimated study flowchart in Figure 1.

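### Adjusting for every minimization factor brings ungrouped city into models of 54 schools: if fitted as a fixed factor, it costs ANCOVA power and inflates the ordinal model's type I error, by an amount that depends on the unstated number of cities

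*Protocol article*

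**What the plan says.** Randomization and Allocation states that "4 predictors of interest for the allocation will be considered: city, cafeteria administration (school-owned versus outsourced), school scope (public versus private"), the fourth factor being school size split at 500 students. Three factors are therefore binary, while city has neither a number of levels nor any grouping.

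Recruitment and Eligibility Criteria places the schools in a region "which total 36 municipalities according to the last official census". Sampling gives the size for an effect magnitude "of 0.90, 54 schools will be needed, considering 27 for the intervention group and 27 for the control group".

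Statistical Analysis then commits to this: "Unadjusted and adjusted estimates allowing for the potential confounding effects of all minimization factors will be presented for primary and secondary endpoints". For hygiene and the processing score, "analysis of covariance or a generalized linear model with an appropriate link function will be used". For menu composition, "we will use an ordinal logistic regression model to assess between-group differences at follow-up, adjusting for the baseline value of the outcome". No random effect, grouping or exemption is given for city. The text does not say whether the unadjusted or the adjusted estimate leads.

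**The concern.** The ordinary reading of these sentences is that city enters as a fixed factor with one indicator per city beyond the first. With few schools per city, this does two different kinds of harm.

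- **ANCOVA (hygiene, processing score).** A city with a single school is fitted exactly by its own indicator and adds nothing to the treatment comparison. Residual degrees of freedom fall as cities are added. The test stays valid but loses power.
- **Ordinal logistic regression (menu composition, a primary outcome).** Many sparse nuisance parameters in a maximum-likelihood fit push the treatment log odds ratio away from zero, and the usual tests reject too often. This affects validity as well as precision.

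The adjusted analysis is the one that reflects how schools were allocated, so readers may well give it weight.

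**Working it through.** **Inputs.** From the protocol: significance level 5%, power 90%, d = 0.90, 27 + 27 schools, four minimization factors, 36 municipalities in the region. Assumed because not stated: two-sided tests; city as a fixed categorical factor; K cities contributing schools, with K varied; three to five categories for menu composition.

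**The plan's own figure.** The normal approximation gives 2 × (1.960 + 1.282)² / 0.90² = 25.9, so 26 per arm. The exact noncentral t gives 27 per arm (power 0.9006; 26 per arm gives 0.889). The planned 54 is reproduced. It makes no allowance for covariates.

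**Degrees of freedom.** Intercept, arm, baseline and three binary factors use 6, leaving 54 − 6 = 48. City adds K − 1, leaving 49 − K.

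**ANCOVA power.** The noncentrality is δ = d × √v, with residual SD 1. Here v is the variation in the arm indicator left after regression on the other covariates; its maximum is 27 × 27 / 54 = 13.5. Schools were allocated by simulated biased-coin minimization on all four factors.

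- No city: v = 13.0, df 48, δ = 0.90 × √13.0 = 3.24, power 0.89.
- K = 12: v = 11.0, df 37, δ = 2.98, power 0.83.
- K = 24: v = 7.73, df 25, δ = 2.50, power 0.67. The variance of the effect is 13.0 / 7.73 = 1.7 times larger.
- K = 36: v = 4.34, df 13, δ = 1.87, power 0.41.

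| Cities represented | Residual df | Power with city fixed |
|---|---|---|
| none fitted | 48 | 0.89 |
| 6 | 43 | 0.87–0.88 |
| 12 | 37 | 0.83 |
| 18–21 | 31–28 | 0.71–0.76 |
| 24 | 25 | 0.67 |
| about 28 | 21 | 0.59 |
| 30 | 19 | 0.56 |
| 36 (upper limit) | 13 | 0.41 |

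Simulated ANCOVA type I error stayed at 0.04–0.055.

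**Sensitivity of the power loss.** If d is on the raw SD scale and the baseline correlation is 0.5, power is 0.96 without city, 0.92 at K = 12 and 0.79 at K = 24; at correlation 0.7, K = 24 gives 0.92. If cities truly differ (intracluster correlation 0.2), power with city fixed is 0.90 at K = 12 and 0.77 at K = 24. With 10% of schools lost, it is 0.77 at K = 12 and 0.58 at K = 24.

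**Ordinal model, type I error at nominal 0.05 (likelihood-ratio test).**

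| Cities represented | Four categories | Other runs under minimization |
|---|---|---|
| none fitted | 0.06–0.075 | about 0.04–0.08 |
| 6 | 0.089 | 0.07–0.10 |
| 12 | 0.117 | 0.07–0.085 |
| 18–21 | 0.159 (at 18) | 0.13–0.16 |
| 24 | 0.193 | 0.13–0.21 (three or five categories; includes Wald tests) |
| about 28 | – | 0.20–0.21 |
| 36 (upper limit) | 0.303 | 0.34–0.37 |

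Runs had 250 to 1,500 replicates; at 250 the Monte Carlo standard error is about 2 to 2.6 points. With intracluster correlation 0.2 and four categories the error was still 0.12 at K = 12 and 0.19 at K = 24. At d = 0.90 the log odds ratio was about 3.8 with city against 2.0 without when about 28 cities were represented, and 2.1 against 1.7 with 6.

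**Alternatives.** With a random intercept for city (REML), the continuous model had power 0.87–0.93 and type I error 0.04–0.06. The ordinal model with baseline and the three binary factors but no city had error of about 0.05–0.075.

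**The case against.** The strongest reply is that the protocol never says city will be coded as ungrouped indicators. Coding is often left to the analysis plan, and this is a condensed article. That stands as a limit on certainty. However, the text does fix the covariate set as all minimization factors and names model families without a random effect, so a fixed factor is its ordinary reading.

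Second, the driving number is missing. A reader might infer that 36 city levels enter the model, with power near 0.41 and error of 30% or more. The documents do not support this. Thirty-six is the number of municipalities in the region where 330 schools are screened, not the number contributing the 54 randomized schools. With 6 cities the power loss is 1–2 points and the ordinal inflation mild. The document's remarks on the distance between schools make a wide spread plausible but do not count cities.

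Third, unadjusted estimates are promised as well and do not suffer from this problem. A poorly behaved adjusted result would therefore be seen beside a stable one. This stands, and it rules out the inference that the trial's conclusions as a whole are compromised. It does not remove the point, because the text does not rank the two estimates.

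Fourth, the ordinal model runs slightly above 5% even without city, so part of the excess is ordinary small-sample behaviour. This also stands; the comparison should be with about 4–8%, not with exactly 5%.

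**Conclusion.** The point holds conditionally and should be fixed; it is not a fatal flaw. If city is an ungrouped fixed factor, the adjusted ANCOVA loses little power at 6 cities, about 6 points at 12, about 13–18 points at 18–21 and about 22–33 points at 24–30. Its type I error is sound, so for hygiene and the processing score the harm is to precision only. The adjusted ordinal analysis of menu composition has the more serious fault: mild inflation at 6–12 cities (about 7–12%), clear inflation at 18–21 (about 13–17%) and around 20% or more from about 24, with odds ratios too far from 1. At exactly 24 cities the figure varies between 13% and 21% with the number of categories and the test used.

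These sizes assume fixed-factor coding, d on the residual scale, and an unknown number of cities. A strong baseline correlation or real city differences reduce the power loss. City differences did not remove the ordinal inflation in the settings tried.

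**What to change.** Define the adjusted model for each endpoint as arm, baseline outcome and the three binary minimization factors (cafeteria administration, public or private, under 500 or at least 500 students). State that city is not fitted as an ungrouped fixed factor. In the continuous models, take city as a random intercept or as a few prespecified geographic groups. In the ordinal model, use a few geographic groups or omit city; a random intercept was not tested there, so the good result from the continuous model should not be carried over. Report how many cities contributed schools.

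The cost is a change of analysis wording and less complete adjustment for city. No new data are needed. The article says analysis is already under way, so the choice should be documented before results are reported.
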